#### **4.2.2 Predicate FACSCalibur™ Method**

1. Label two BD Trucount™ tubes according to an ID scheme provided to the site by BD..
2. Prepare samples for the predicate system as follows (see the BD Tritest™ CD3/CD4/CD45 Reagent package insert for additional information):
  - Pipette 20 µL of BD Tritest™ CD3/CD4/CD45 Reagent into each labeled Trucount™ tube, being careful not to touch the Trucount™ bead pellet (according to the package insert).
  - Thoroughly mix the WB specimen by gentle inversion and pipette 50 µL (using reverse pipetting) into each Trucount™ tube.
  - Cap each tube and vortex to mix.
  - Incubate the tubes in the dark at room temperature (i.e., 20 to 25 °C) for 15 minutes.
  - Pipette 450 µL 1X BD FACS Lysing Solution into each tube.
  - Cap each tube and vortex to mix.
  - Incubate in the dark at 20 to 25 °C for 15 minutes.
3. Acquire the BD Trucount™ tubes on the FACSCalibur™ immediately (vortex prior to acquisition) or store in the dark at 20 to 25 °C. Acquire within 24 hours of blood draw..
4. Review the dot plots and verify that at least twenty five hundred (2,500) lymph events have been collected, to consider the predicate data “evaluable”.

#### **NOTES:**

- *Re-analysis of a sample is allowed. A sample can be acquired two times.*
- *BD MedLab will be the sole site that will use venous blood manipulated samples to test Hb concentration*

#### **4.2.3 Predicate Hb Method**

- Label two microcentrifuge tubes according to the ID scheme provided to the site by BD before transferring the blood
- Select whole blood mode

- Mix the specimen by inverting the tube 10 times
- Transfer 100µL into a minicentrifuge tube
- Acquire sample
- For the next sample, mix specimen by inverting the tube 10 times, transfer 100mL into a microcentrifuge and acquire the sample.
- Print sample results

#### **4.2.4 Enrolled Sample Acquisition and Analysis**

##### **4.2.4.1 BD FACSPresto Method**

- Enter the specimen ID and date information using the touch screen
  - Once incubation is finished, load the investigational cartridge into the instrument.
  - The instrument will automatically read and calculate Abs CD4, %CD4 and Hb concentration.
  - Print sample results. Review results, if there is quality control message , refer to IFU for troubleshooting
  - Repeat steps with second replicate cartridge

##### **4.2.4.2 Predicate FACSCalibur™ Method**

- Acquire the BD Trucount™ tubes on the FACSCalibur™ immediately (vortex prior to acquisition) or store in the dark at 20 to 25 °C.
- Acquire within the timeframes specified in the BD Tritest™ reagent package insert.
- Print and review results

##### **4.2.4.3 Predicate Hb Method**

- Place the well mixed and uncapped specimen under the aspiration probe and analyze
- When the analysis is complete, review and print results
  - Write results onto the corresponding CRF
  - Repeat procedure with a second tube

##### **4.2.4.4 All Methods**

Review the acquisition data for acceptability (see Section 7.3 for further details) and, if no reacquisition is required, discard the IUO vials and IVD tubes.

**Figure 4: Enrolled Specimen Testing**

[figure not shown]

#### **4.2.5 Customer's Ease of Use**

Ease of Use the PEO/IUO BD FACSPresto System will be evaluated in a minimum of 2 operators per site after they have completed Proficiency Training and before the start of enrollment. Ease of Use Assessment will be done using a survey addressing specific aspects of the functionality of the PEO/IUO BD FACSPresto System and BD CD4/%CD4/Hb cartridge. The operators will complete and return the Eases of Use survey to BD.

Ease of use survey will consist of questions addressing workflow and functionality of the PEO/IUO BD FACSPresto System. Each question will have 6 possible answers with a numeric value assigned for analysis. Example of the answers as the following:

- Extremely easy/satisfied, numeric value =5
- Somewhat easy/satisfy, numeric value =4
- Neutral, numeric value =3
- Slightly difficult/ dissatisfied, numeric value =2
- Very difficult/ dissatisfied, numeric value =1
- Not applicable (NA), numeric value =0

### **5.0 DISCONTINUATION OF SPECIMEN TESTING**

Post-enrollment, instances may occur that will require the discontinuation of the WB specimen testing such as:

- If further visual inspection of an enrolled specimen reveals clotting and/or hemolysis that initially were not apparent, this specimen would be unsuitable for study testing or, if results have been generated, these results would not be included in analysis.
- If an enrolled specimen (of sufficient quality) is broken/spilled, this “quality not sufficient (QNS)” specimen would require discontinuation of study testing
- If an enrolled specimen (with adequate time post-draw to enroll for study testing) cannot be stained within 24 hrs due to unanticipated testing difficulties, this specimen would require discontinuation of study testing and document reason for withdrawal.

### **6.0 PRODUCT ERRORS/ DEFECTS/ FAILURES**

Errors, defects or unanticipated failures observed for the investigation study product(s) will be documented using the study error forms and communicated immediately to the Study Monitor.

These events will be documented and escalated in accordance with BD internal procedures.

### **7.0 DATA COLLECTION AND MANAGEMENT**

#### **7.1 Data Collection and Source Documents**

Study data will be collected in the form of standardized case report forms (CRFs)/ electronic CRFs (eCRF) and other data collection forms that will be provided for use at all investigational sites. Instrument data will also be collected in the form of instrument records (electronic files or printouts) such as from instrument set-up and sample acquisition results in different file formats (CSV, EXP, PDF, FCS, daily summary in Excel spreadsheet, etc.) are considered source documents.

Source documents may also include supporting medical records and informed consents, diagnostic test results from other laboratory equipment, or even CRFs, when the original collection of data is done directly on the case report form. Investigators will maintain all source documents associated with the protocol, including laboratory results and instrument reports. All hard copy and electronic data will be secured to ensure confidentiality. The source documents will be used for study monitoring and data management review to verify study compliance.

In verifying data integrity, the monitor will ensure that the data in the CRFs are consistent with protocol requirements. It is not necessary for every data entry point captured on a CRF to have a matching source, however, where data appears in both, they must agree.

## **7.2 Submission of Data Packages to Sponsor**

Investigators are responsible for the collection, review, and timely submission of all required study data to BD for processing, including instrument electronic files, which will be acquired and saved in specified study archives.

It is anticipated that each site will provide daily update of the acquired data according to the process that the sponsor will define during site initiation and training.

All study data that include paper and electronic documentation of the study, will be submitted to BD in a weekly package by courier. The PI or designee will ensure that the data and documentation are accurate, complete, and in compliance with applicable documentation requirements, prior to assembling and submitting data packages to BD.

BD will provide a checklist during site initiation and training that can be referenced during data package compilation and review. This checklist may contain, but not be limited to:

- List of the minimum required package items
- Key elements from the user documentation to be referenced for:
  - Data evaluation (e.g., flagged due to low lymphocyte events)
  - Predicate evaluation of plots (e.g., sub-optimal resolution of specified populations)
  - Instrument printouts

Quality assurance procedures should be followed to ensure that complete, accurate and timely data are submitted, that protocol requirements are followed, and that product failures, errors, adverse events and adverse device effects are detected, managed and reported as required, if applicable.

Upon completion of data package review, the site will forward this package to BD in regular shipments at intervals agreed upon by the CRA and PI (typically, once per week).

**Figure 6: Study Data and Submission to BD**

[figure not shown]

### 7.3 Data Evaluation for Inclusion/Exclusion from Analysis

After receipt of data packages from the sites, the BD CRA/study monitor or designee will review the contents to ensure that the data are accurate, complete, and in compliance with all applicable requirements.

In instances where data is found to be missing or incomplete, the CRA will contact the site to resolve data discrepancies using a data clarification form (DCF) for query resolution.

Discrepancies may be addressed via calls to the investigational sites or during visits by site monitors. Based on the outcome of this review, the CRA may identify and provide a reason for specified data to be deemed not evaluable and possibly excluded from analysis (but not removed from the study database).

BD has targeted a minimal and maximum number of specimens to enroll based on age and CD4 bins (see section 4.2 Specimen Enrollment). As data is reviewed and all queries resolved, BD will track the number of evaluable specimens in each CD4 bin. When the evaluable number reaches the target number within each bin, BD will notify the sites so that specimens can preferentially be enrolled for other bins.

In the case of excess data points for any bin, data for any other specimens enrolled in that bin will be excluded from the final data analysis (but not from the study database). When selecting between multiple data points for inclusion in the final analysis, the data with an earlier enrollment date will be given preference.

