#### **8.2 Eligibility, Exclusions, Missing Data, Interim Analysis**

All specimens meeting the eligibility criteria and tested with the BD FACSPresto System will be analyzed for primary and secondary endpoints. It is anticipated that a minimum of 80% of the data will from matching venous and capillary blood specimens from the same subject for analysis. Management of dropouts and missing data will depend on their frequency and the particular outcome measure; any such adjustments will be described completely and documented. All valid data will be included in the analysis; if outliers are determined to exist, the monitor will investigate the identified outliers.

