### **8.6 Methods to Reduce Bias**

Blinding of diagnostic results from study personnel is facilitated by the de-linking process during study enrollment: study personnel who have access to subject information will not be involved in acquiring or analyzing specimens. The site personnel who will perform sample preparation and acquisition will have study-specific training to ensure consistent techniques to minimize bias.

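### Section 7.3 lets the sponsor's CRA exclude data for any stated reason without masking to the paired results, which undercuts the Section 8.2 commitment to include all valid data

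*Protocol*

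**What the plan says.** **Who decides.** Under Protocol Section 7.3 the sponsor's CRA/study monitor, or a designee, reviews each site's package for accuracy, completeness and compliance. After that review, "the CRA may identify and provide a reason for specified data to be deemed not evaluable and possibly excluded from analysis". Such data are excluded "but not removed from the study database".

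**What the reviewer receives.** Section 7.2 states: "All study data that include paper and electronic documentation of the study, will be submitted to BD in a weekly package by courier". Instrument files are included, and in addition "each site will provide daily update of the acquired data".

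**What is promised.** Section 8.2 states: "All specimens meeting the eligibility criteria and tested with the BD FACSPresto System will be analyzed for primary and secondary endpoints". It continues: "All valid data will be included in the analysis; if outliers are determined to exist, the monitor will investigate the identified outliers". It does not define an outlier or say what follows from the investigation.

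**Masking.** Section 8.6 is the only masking text: "Blinding of diagnostic results from study personnel is facilitated by the de-linking process during study enrollment". It adds that staff with access to subject information do not acquire or analyse specimens.

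**Refilling of bins.** Section 7.3 also has the sponsor count evaluable specimens per CD4 bin and redirect enrolment once a bin's target is met.

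**The concern.** The accuracy claim rests on pairs of results. The person who may rule a result out works for the sponsor, holds both methods' records and is not told to ignore the difference between them. A pair that disagrees badly invites a search for a reason, while a pair that agrees does not. Each reason found may be genuine and the selection still one-sided. Since an excluded specimen does not count towards its bin, enrolment can refill the slot, and the final 400 would look complete.

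The acceptance criteria in Section 8.5 are fixed limits: for Abs CD4, a 95% CI for the Deming slope within 0.9 to 1.1, R2 of at least 0.9 and an intercept within ±20. If true agreement is near those limits, a few exclusions can decide the result that goes into the regulatory submission.

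**Working it through.** **1. The plan's own figures.** The 400 specimens agree with the bins (4 × 100) and with the sites (133 + 134 + 133). No SD, power or expected exclusion rate is given, so no stated figure can be tested. Everything below is a what-if.

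**2. The passages side by side.** Section 8.2 includes all valid data. Section 7.3 leaves the CRA to say what is evaluable. Section 4.2.4.4 refers to 7.3 for the acceptability of acquisition data, but 7.3 gives no criteria. Section 8.7.2 refers to 8.2 for the exclusion details, and they are not there. The commitment in 8.2 is therefore only as firm as the open discretion in 7.3.

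**3. Model for Abs CD4.** Assume 100 specimens per bin, uniform within the bin, with the top bin ending at 2000 or at the protocol's 5000. Error is proportional and equal in both methods. The Deming error ratio is 1, with a jackknife SE. There are 400 simulated studies per row.

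*Check of R2 by hand* (top bin to 2000, true slope 1.0). The bin means are 150, 375, 750 and 1500, with overall mean 693.75. The within-bin means of x² are 25,833, 145,833, 583,333 and 2,333,333, which average 772,083. Var(x) = 772,083 − 693.75² = 290,794. A paired CV of 15% gives an error variance per method of (0.15²/2) × 772,083 = 8,686. R2 = (290,794/299,480)² = 0.943, as simulated. A paired CV of 25% gives 24,128 and (290,794/314,922)² = 0.853, against 0.854 simulated.

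*Check of the slope criterion by hand* (true slope 0.92, CV 15%, top bin to 2000). The lower confidence limit must reach 0.9.
- All data: mean slope 0.920, SE 0.0175. The slope needed is 0.9 + 1.96 × 0.0175 = 0.934; z = (0.934 − 0.920)/0.0175 = 0.82; probability about 0.21 (simulated 0.18).
- After dropping the 10 largest absolute differences: mean slope 0.947, SE 0.0147. The slope needed is 0.929; z = −1.24; probability 0.89 (simulated 0.89).

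**4. Chance of meeting all three Abs CD4 criteria, dropping the largest absolute differences**

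| True slope, paired CV, top bin | 0 dropped | 10 | 20 | 40 |
|---|---|---|---|---|
| 0.92, 15%, 2000 | 0.17 | 0.81 | 0.82 | 0.60 |
| 0.92, 15%, 5000 | 0.11 | 0.56 | 0.39 | 0.09 |
| 1.0, 25%, 2000 | 0.00 | 0.30 | 0.83 | 0.99 |
| 1.0, 25%, 5000 | 0.37 | 0.78 | 0.86 | 0.95 |
| 1.0, 15%, 2000 | 0.97 | 0.99 | 1.00 | 1.00 |
| 1.0, 15%, 5000 | 0.90 | 0.97 | 0.98 | 1.00 |

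The Monte Carlo SE is at most √(0.25/400) = 0.025.

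**5. Sensitivity to the ranking.** A separate run of the first row with 10 dropped gave 0.18 to 0.80 by absolute difference, but only 0.17 to 0.32 by percent difference.

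**6. The intercept on its own.** Assume CVs of 6% (predicate) and 10% (device), 1,000 studies, and 5% (20 of 400) dropped. With a true intercept of +30, the chance of meeting ±20 goes from 0.29 to 0.47 by percent difference, but from 0.29 down to 0.02 by absolute difference. With +25 it goes from 0.58 to 0.70, or down to 0.16. The intercept also explains the falls in the first two table rows: with the top bin at 5000 its mean moves from 1.0 to −16.1, −23.3 and −28.9 as 10, 20 and 40 pairs are dropped.

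**The case against.** The protocol is not without safeguards. Section 8.2 commits to analysing every eligible tested specimen. Section 7.3 requires a reason and keeps excluded data, so a later all-data analysis is possible. The stated standard of review is accuracy, completeness and compliance, not agreement between methods. Objective grounds exist: at least 2,500 lymphocyte events (4.2.2), clotting or haemolysis, spillage and the 24-hour staining limit (5.0), and earlier enrolment date for bin surplus (7.3). A numerical outlier rule or a sensitivity analysis may stand in the SAP, so their absence from the protocol is not counted here.

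All of that stands, and it rules out several stronger readings that a reader might infer:
- *That outliers will be deleted.* The text provides only for investigation.
- *That there is no masking.* There is some at the sites; what is missing is masking of the sponsor's reviewer.
- *That no all-data analysis is planned.* Section 8.2 promises one in principle.
- *That the CRA is stated to compare the two methods.* This is inferred from what the packages contain. That the monitor in 8.2 is the reviewer in 7.3 is likewise the natural reading, not an explicit statement.
- *That every criterion improves when discordant pairs go.* Step 6 shows that the intercept can move either way.

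What the safeguards do not do is close the list. Section 7.3 is not confined to the objective grounds, and Section 5.0 allows clotting or haemolysis to be invoked after results exist. Giving a reason makes an exclusion traceable; it does not make the search for reasons even-handed. Who decides, when, and with what in view is an operational rule that this protocol itself sets.

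**Conclusion.** The point holds as a defect in the exclusion rule, not as evidence that data will be removed selectively. An open-ended decision by an unmasked sponsor reviewer undercuts the inclusion commitment in Section 8.2.

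The size depends on assumptions about SD, true bias and how discordance is judged, none of which the protocol gives. In borderline cases, dropping 10 to 20 of 400 pairs (2.5 to 5%) can turn a likely failure on the slope interval or R2 into a likely pass. With slope 0.92, CV 15% and the top bin to 2000, the rise is large under absolute ranking and modest under percent ranking. With no true bias and CV 15%, the pass rate is already 0.90 to 0.97 and exclusions matter little. The rule should be changed before data review, but no stated figure in the plan is wrong.

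**What to change.** **In Section 7.3**
- Limit exclusions to the technical grounds the protocol already uses: QC failure or instrument message, fewer than 2,500 lymphocyte events, clotting or haemolysis, spilled specimen, staining beyond 24 hours, and bin surplus by enrolment date.
- Record the evaluability decision for each method's record before the two methods' results are paired.

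**In Section 8.2**
- State that an outlier investigation cannot by itself remove a pair.
- Correct the cross-references in 4.2.4.4 and 8.7.2 so that both lead to the closed list.

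**In reporting** (protocol or SAP)
- Give the Section 8.5 criteria also on all eligible specimens with results from both methods.
- List every exclusion with its reason.

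**Cost.** Data review is reordered and one analysis is added; no further specimens are needed. Both methods' files now arrive in one package, so they would have to be separated or read by different people; the documents do not show whether present staffing covers that. Genuine errors that can be recognised only by their discordance would stay in the main analysis.

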#### **7.4 Data Management and Storage**

BD Data Management will be responsible for the entry, processing and maintaining of study data. All original CRFs will be sent to BD as part of the periodic submission package or be retrieved by the site monitor with a copy kept at the site. BD Data Management will process the data and will carry out edit checks, error checks and audits, if needed. The Investigator will be queried on issues concerning data completeness and consistency.

All above-mentioned tasks will be performed according to the Sponsor's relevant internal procedures; ensuring adherence to GCPs. Audits may be performed for quality assurance of data handling.

### **8.0 STATISTICAL METHODS**

Statistical analyses will be conducted by the BD Biostatistics group.

#### **8.1 Sample Size Determination**

For the Accuracy procedure, a sample size of 400 pediatric, adolescent and adult patient WB specimens, from the study site that provide valid results (i.e. meeting enrollment and protocol testing criteria) will be required to determine the bias (expected difference) between the "PEO/IUO" system versus the predicate systems.

#### **8.2 Eligibility, Exclusions, Missing Data, Interim Analysis**

All specimens meeting the eligibility criteria and tested with the BD FACSPresto System will be analyzed for primary and secondary endpoints. It is anticipated that a minimum of 80% of the data will from matching venous and capillary blood specimens from the same subject for analysis. Management of dropouts and missing data will depend on their frequency and the particular outcome measure; any such adjustments will be described completely and documented. All valid data will be included in the analysis; if outliers are determined to exist, the monitor will investigate the identified outliers.

#### **8.3 General Statistical Considerations**

All statistical analyses will be performed using commercially available statistical software. Adequate source document verification and/or audit activities will be utilized to assure the validity of study conclusions. Analysis shall be performed based on methods described in statistical analysis plan or methods described in section of the Analysis Method of the protocol. All related and resulting reports, documents and data shall be produced and maintained in such a way as to ensure their control and the protection of subject privacy as far as is reasonably practicable. Data files and analytic reports will be archived according to requisite regulatory standards.

#### **8.4 Study Endpoints / Outcome Measures**

#### **8.4.1 Primary Endpoint**

The primary endpoint is the bias (expected difference) between the investigational system versus the predicate system measured as Abs CD4 and %CD4 in peripheral venous blood specimens from a minimum of 400 specimens with valid results tested at three or more sites.

#### **8.4.2 Secondary Endpoint**

Secondary endpoints have been defined for the analysis of the AbsCD4, %CD4 and Hb results from investigational BD FACSPresto System and predicate methods using capillary and venous blood.

##### **8.4.2.1 Evaluation of CD4 and Percentage of CD4 in capillary blood**

Expected difference between the investigational system using capillary blood specimens versus the predicate system using venous blood specimens measured as AbsCD4 and %CD4.

##### **8.4.2.2 Evaluation of Hb concentration in venous and capillary blood**

Expected difference between the investigational system testing capillary blood specimens versus the predicate system using venous blood specimens measured as Hemoglobin concentration.

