## 2.2 Secondary Objective(s)

1. The secondary objective of this study, enshrined within phase III are the following:  
Determine method bias between the PEO/IUO labeled BD FACSPresto System versus the predicate system in the determination of Abs CD4 and %CD4, using capillary blood in de-identified specimens at three or more external study sites.
2. Determine the method bias between the PEO/IUO BD FACSPresto System versus the predicate system for Hb, Sysmex (KX-21) hematology analyzer, in the determination of Hb concentration using venous blood and capillary blood in de-identified specimens.
3. Evaluate the customer's ease of use of the IUO PEO/IUO BD FACSPresto System following brief training.

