**4.1.6 Enrollment by Hb (only venous blood)**

For Hb binning assignment will be done using the first replicate from the predicate method (Sysmex KX-21), Hb enrollment will follow the binning shown below.

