#### **Hb in venous and capillary blood**

- For Hb, the the 95% confidence interval for the slope estimated using Deming Regression shall be within 0.9 to 1.1 when regressing the investigational device to the predicate device. The R2 from the Deming regression shall be  $\geq 0.9$ . The intercept estimated from the Deming Regression shall be within  $\pm 0.5$  g/dL.
- For capillary blood Hb concentration, the mean difference (bias) for samples with Hb concentration of  $10.5 \pm 1$  g/dL (clinical decision point) between the BD FACSPresto System result and the predicate system result shall be  $< 7\%$ , with  $> 95\%$  confidence, with respect to specimens typical in the target markets.

OR

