### 8.7.2 Secondary Endpoints CD4 and Hb Binning

The secondary endpoint binning for AbsCD4 and %CD4 in capillary blood will apply the same bins described for CD4 in venous blood in section 8.7.1.

The secondary endpoints will address Hb bias determination between the investigation and predicate methods using venous blood. Additional bias analysis will be required around the clinical decision point of 10.5 (9.5-11.5) for determination of Hb in capillary blood using investigational versus the predicate method using venous blood. Three bins have been defined for Hb.

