#### Clinical Decision Points for HB (Only capillary blood)

| Bins (g/dL)                    | Total # Desired | Minimum   |
|--------------------------------|-----------------|-----------|
| <math>4.5 \pm 1</math>  | 60       | 40 |
| <math>10.5 \pm 1</math> | 60       | 40 |
| 17                      | 60       | 40 |

For each specimen, the mean differences between investigational and predicate results (for both Abs CD4 and %CD4), will be calculated and pooled across all specimens to produce a mean difference. Estimates from the Deming regression will be used to evaluate the equivalency between the investigational and predicate systems, according to the acceptance criteria presented in Section 8.5

It is anticipated that the total number of enrolled specimens will exceed 400 in order to achieve the required number of evaluable specimens in each age and CD4 bin.

For each Hb specimen, the mean differences between investigational and predicate results will be calculated and pooled across all specimens to produce a mean difference. Bias analysis at the clinical decision point of  $10.5 \pm 1$  will be used to evaluate the equivalency between the investigational and predicate systems, according to the acceptance criteria presented in Section 8.4. Additional analysis at  $4.5 \pm$  and  $17 \pm 1$  may be included for information only

Note that when the number of evaluable specimens reaches the desired target within each CD4 bin, data for any remaining specimens enrolled in that bin may be excluded from final data

analysis (see Data Evaluation for eligibility from Analysis in section 8. 2for details). BD will track bin enrollment during the course of the study and will notify sites when a target for any bin has been reached, so that sites can preferentially enroll specimens for other bins.

Ease of Use data will be discrete and qualitative variables obtained from small number of individuals at the participating clinical sites in the study. Data will be summarize and presented in tables or graphs. Additional statistical analysis is anticipated to be limited. Note that a subset of the total Accuracy data (i.e., from the site enrolling the most specimens) may be analyzed separately for the purpose of updating the technical file for CE declaration.

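### The protocol defines the Hb secondary endpoint for different specimen types in different sections, and its Hb acceptance criteria do not say which specimens they judge or whether both are required.

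*Protocol*

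**What the plan says.** The objective (Protocol 2.2, item 2, and the Protocol Summary) is Hb bias against the Sysmex analyzer "in the determination of Hb concentration using venous blood and capillary blood in de-identified specimens".

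The endpoint (8.4.2.2, repeated in the Summary) is headed "Evaluation of Hb concentration in venous and capillary blood", but its only content is "Expected difference between the investigational system testing capillary blood specimens versus the predicate system using venous blood specimens measured as Hemoglobin concentration".

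Section 8.7.2 describes the endpoint differently: "The secondary endpoints will address Hb bias determination between the investigation and predicate methods using venous blood". It then adds: "Additional bias analysis will be required around the clinical decision point of 10.5 (9.5-11.5) for determination of Hb in capillary blood". The heading of 4.1.6 limits the Hb range bins to venous blood. Capillary blood has its own bins at 4.5, 10.5 and 17 g/dL, with a minimum of 40 each.

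For acceptance, 8.5.2 has a joint heading for venous and capillary Hb with two bullets. The first begins "For Hb, the the 95% confidence interval for the slope estimated using Deming Regression shall be within 0.9 to 1.1" and adds R2 of at least 0.9 and an intercept within ±0.5 g/dL. It names no specimen type. The second is capillary only: mean difference below 7% at 10.5 ± 1 g/dL with more than 95% confidence. The word OR follows, with nothing after it.

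Section 8.7.2 also states: "For each Hb specimen, the mean differences between investigational and predicate results will be calculated and pooled across all specimens to produce a mean difference". It judges equivalency by the bias at 10.5 ± 1 g/dL under criteria it places in section 8.4, whereas they stand in 8.5. It leaves 4.5 and 17 g/dL for information only. The table in 4.1.6 puts that mark on all three decision points, including 10.5.

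**The concern.** The protocol itself fixes the endpoints and acceptance limits, so they should lead to one analysis. As written, two analysts could reach different Hb verdicts from the same data while each followed the text.

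Fingerstick blood is a central specimen for a point-of-care device, and the accuracy data are meant to support the CE and 510(k) submissions. What is at stake is whether capillary Hb must meet a limit across the measuring range, only near 10.5 g/dL, or, depending on what the OR was meant to introduce, not necessarily any limit of its own.

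**Working it through.** **1. The passages side by side**

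| Place | Device specimen for Hb |
|---|---|
| 2.2 objective 2; Summary objectives | venous and capillary |
| 8.4.2.2 heading | venous and capillary |
| 8.4.2.2 definition; Summary endpoint | capillary only |
| 4.1.6 range bins | venous only |
| 8.7.2 opening text | venous, with capillary additional near 10.5 g/dL |
| 8.5.2 Deming bullet | not stated |
| 8.5.2 bias bullet | capillary, 10.5 ± 1 g/dL |

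For CD4, 8.5.1 gives the limits for the venous primary endpoint and 8.5.2 repeats them expressly for capillary blood. Hb has no such split.

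**2. What each reading of the Deming bullet implies**

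- Applied to each specimen type: both are tested over the range and nothing is masked.
- Venous only (fits 8.7.2): capillary rests on the 10.5 rule alone.
- Capillary only (fits the 8.4.2.2 definition): venous Hb has no limit.
- Both pooled in one fit: capillary error is averaged with venous results.

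**3. Size under the pooled or venous-only reading**

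The protocol gives no Hb variance or power figure to reproduce, so this is an illustration.

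Inputs from the protocol: 400 specimens in Hb bins of 140/180/80 (4.1.6); slope CI within 0.9 to 1.1, R2 at least 0.9, intercept within ±0.5 g/dL, and the 7% rule (8.5.2).

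Assumptions: values uniform within bins; predicate SD 0.2 g/dL; venous unbiased with SD 0.2 to 0.4; capillary SD 0.3 or 0.6; Deming error ratio 1; jackknife CI; one-sided 95% limit for the 7% rule.

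Illustrative capillary line: 0.90 + 0.86 × Hb, so bias = 0.90 − 0.14 × Hb.

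- 4.5 g/dL: 0.90 − 0.63 = +0.27, or +6.0%
- 10.5 g/dL: 0.90 − 1.47 = −0.57, or −5.4%
- 17 g/dL: 0.90 − 2.38 = −1.48, or −8.7%

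Alone, slope 0.86 and intercept 0.90 both lie outside the limits. Averaged with an unbiased venous line, the slope is about (1 + 0.86)/2 = 0.93 and the intercept about 0.90/2 = 0.45, both inside. Fitted values differ slightly because of measurement error.

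Simulated results for this line:

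- Capillary alone meets the Deming limits in 0% of runs.
- The pooled fit meets them in 99.5% to 100%.
- Pooled fit and 10.5 rule are both met in about 64% (capillary SD 0.6) to 98% (SD 0.3).
- The 10.5 rule by itself, at SD 0.6, is met in about 51%, 67% and 77% of runs with 40, 60 and 80 specimens in the band. With a two-sided 95% interval these become 38%, 54% and 67%.

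Under the venous-only reading the venous fit passed in every run, so the chance of escape equals the pass rate of the 10.5 rule.

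Other lines, in 400 runs each, using every specimen in the 9.5 to 11.5 band:

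| Capillary line | Capillary Deming | Pooled Deming | 10.5 rule | Pooled and 10.5 met, capillary Deming failed |
|---|---|---|---|---|
| 0.50 + 0.90 × Hb | 6–21% | 100% | 87–100% | 69–94% |
| 0.60 + 0.88 × Hb | 0% | 100% | 36–67% | 36–67% |
| 0.88 × Hb (12% low throughout) | 0% | 100% | 0% | 0% |

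The last row shows why the OR matters. If the 10.5 rule is mandatory, it catches a uniform 12% deficit. If it is an alternative to a pooled or venous Deming pass, it does not.

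**The case against.** A reader might infer that venous and capillary Hb pairs go into one regression, so that venous results will hide a failing capillary result. The documents do not support that. No section describes such a regression. The pooling sentence in 8.7.2 concerns mean differences, and equivalent wording is used there for CD4, whose specimen types are judged separately. Separate bins, and a capillary bullet distinct from the general Hb bullet, point if anything towards separate handling.

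Two other strong statements also go too far. Venous Hb is not absent: it appears in the objective, two headings and 8.7.2, and what it lacks is a definition in 8.4.2.2. Capillary Hb at 4.5 and 17 g/dL is not ignored: bins are planned there and analysis may be reported. What is missing is a pass/fail limit, which can be a legitimate design choice.

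The illustrative line is also a chosen one. Its offsetting slope and intercept keep the 10.5 g/dL bias under 7%, and with SD 0.6 and 40 specimens the existing rule still rejects it about half the time.

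Finally, 8.3 refers to a statistical analysis plan that may say how regressions are split. That plan can supply detail, but the conflict between the protocol's own objective, endpoint and binning text would remain, as would the unfinished criterion. These parts of the concern stand.

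**Conclusion.** The inconsistency is on the page and needs no assumption: 2.2, 8.4.2.2 and 8.7.2 give three different scopes for the Hb endpoint. The Deming criterion names no specimen type, and the 10.5 g/dL criterion is at once a judged criterion, an item for information only, and one side of an unfinished alternative.

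The consequence is conditional. If the Deming limits apply to each specimen type, nothing is masked. If they are read as pooled or venous-only, a capillary bias away from 10.5 g/dL can meet every written limit. For the illustrative line this happens in roughly 64% to 98% of runs under the pooled reading with the 10.5 rule required. That range depends on the assumed SDs, the chosen bias line and the number of specimens in the decision band. It shows what the wording permits and does not predict how the device will perform.

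**What to change.** - In 8.4.2.2 and the Summary, define two Hb endpoints: device venous versus Sysmex venous, and device capillary versus Sysmex venous.
- In 8.5.2, apply the slope, R2 and intercept limits to each separately, as for CD4, and state that the two specimen types are not combined in one regression or mean difference.
- State whether the capillary criterion at 10.5 ± 1 g/dL is required in addition, and complete or delete the OR.
- Reconcile the information-only mark in 4.1.6 with 8.7.2, align the opening text of 8.7.2 with the two endpoints, and correct its reference from 8.4 to 8.5.

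The cost is protocol wording and one more regression on data already planned, since both specimen types are run on the device. The one real downside for the sponsor is that capillary Hb must then pass on its own.
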